Recently, Kourouche proposed a concept of the “ChIP” bundle treatment protocol for BCT, which involved respiratory support, analgesic medications, preventative therapies, and surgical treatments [10]. In this protocol, high-flow nasal cannula oxygen therapy (HFNC) is used, which is an emerging type of respiratory support system which can provide high-flow mixed gases through special nasal cannulas with higher temperature and humidity than standard nasal cannulas. HFNC is the preferred method of respiratory support in the ChIP bundle. It was reported that the application of the ChIP protocol reduced the incidence of pneumonia in patients with BCT by 56% [11]. However, no research to date has confirmed the contribution of HFNC to this protocol.

Up to now, there have been only two small retrospective studies exploring the application of HFNC in BCT. One study showed that 18% of 105 patients with moderate to severe BCT [Abbreviated Injury Scale (AIS) chest score ≥ 3] received endotracheal intubation due to treatment failure with HFNC [12]. This rate is similar to the 12–18% NIV failure rate previously reported in the literature [8]. In another retrospective study, compared with standard oxygen therapy, HFNC significantly reduced both the intubation rate and the ICU length of stay in patients with moderate to severe BCT [13]. However, to the best of our knowledge, there are no published studies directly comparing the efficacy of HFNC to NIV in patients with BCT. The present protocol is conceived to test the hypothesis that HFNC is non-inferior to NIV in reducing treatment failure in moderate to severe BCT patients with acute respiratory failure.

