### Study groups

Within 3 h of meeting inclusion criteria and obtaining informed consent, patients will be randomly allocated to receive either NIV or HFNC. Patients randomized to the HFNC group will receive HFNC (AIRVO™ 2, Fisher & Paykel Healthcare, Auckland, New Zealand) using suitable large-bore nasal prongs selected according to the size of the patients’ nostrils. The initial airflow will be set at 50 L/min and adjusted according to patient tolerance. To reach an absolute humidity of 44mg H_2_O/L, the temperature will be set to 37°C. FiO_2_ will be initially set at 1.0 and adjusted to maintain a SpO_2_ ≥ 92%. HFNC will be continuous if it is well tolerated, or it can be used intermittently according to clinician decision. During the termination of HFNC, standard oxygen therapy will be used to maintain a SPO_2_ ≥ 92%.

Subjects randomized to the NIV group will receive NIV (BiPap Vision or PHILIPS V60) in spontaneous or timed (S/T) mode using a standard oral-nasal (full-face) mask (RT040). The parameters will be adjusted adaptively: the expiratory positive airway pressure (EPAP) settings will be increased gradually from 4 cmH_2_O to make sure the patient can trigger the ventilator with each inhalation. The inspiratory positive airway pressure (IPAP) will be initially set to 8 cmH_2_O and gradually increased to achieve a satisfactory tidal volume (8mL/kg) with acceptable tolerance. The pressure level and FiO_2_ will be adjusted to maintain a respiratory rate ≤ 28/min and a SpO_2_ ≥ 92%. The NIV should be applied as continuously as possible for 24 h. To improve tolerance, a short break from NIV will be allowed with the consent of the attending physician. Oxygen therapy during any interruption of NIV will be the same as for the HFNC group.

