### Statistical analysis and sample-size calculation

Reported intubation rates in BCT patients receiving NIV range from 12 to 18% [8], so the sample size is estimated assuming a baseline failure rate (including modality switch) of 18–23% for each group and a predefined non-inferiority margin of 9% for HFNC. We set the non-inferiority margin according to relevant data [18, 19], and after discussion with three senior pulmonologists. We computed a sample size of 488 patients in this trial, using an *α* = 0.05 (one-sided) and *β* = 0.20, with a non-inferiority limit of 9%. After considering a potential patient dropouts and nonparametric analysis, 562 patients (281 per modality) will be the target sample size for this trial.

All statistical analyses will be performed on an intention-to-treat basis by an independent investigator who is blinded to treatment allocation. The Kolmogorov–Smirnov test will be used to test the normal distribution of data. Normally distributed data will be expressed as means ± standard deviation, while skewed distributed data will be reported as medians with interquartile (25th–75th) percentiles. The two modality groups will be compared using *t*-tests or Mann–Whitney *U*-tests. Numeric data will be presented as a percentage (%), using chi-squared or Fisher’s exact probability tests. Significance will be set at < 0.05 and all data analysis will be conducted with SPSS 26.0 (IBM Corporation, Armonk, NY, USA).

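### Intention-to-treat is fixed as the only basis for every analysis of a non-inferiority trial; a per-protocol analysis against the same 9% margin should stand beside it

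*Protocol article*

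**What the plan says.** The hypothesis, in the Background, is that "HFNC is non-inferior to NIV in reducing treatment failure in moderate to severe BCT patients with acute respiratory failure". The section on statistical analysis and sample size sets "a predefined non-inferiority margin of 9% for HFNC" and then says: "All statistical analyses will be performed on an intention-to-treat basis by an independent investigator who is blinded to treatment allocation". No per-protocol, as-treated or sensitivity set is named anywhere in the article.

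Four other statements bear on the point:

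- **Outcomes.** Failure is intubation with invasive ventilation, or a change from one device to the other, followed for 28 days. A switch is therefore an event in the primary analysis.
- **Study groups.** HFNC is continuous if tolerated, or "it can be used intermittently according to clinician decision". Short NIV breaks are allowed with the attending physician's consent. Off the device, both arms receive the same oxygen therapy.
- **Sample size.** The computed 488 is raised to 562 with the words "After considering a potential patient dropouts" and a reference to nonparametric analysis. No dropout rate is given, nor how dropouts enter the intention-to-treat analysis.
- **Data collection and Study organization.** Device settings, intolerance, switches with their times and reasons, and protocol deviations are all recorded. None of these feeds a stated analysis set.

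**The concern.** In a superiority trial, intention-to-treat is usually the cautious choice, because imperfect delivery shrinks the difference that the sponsor hopes to show. In a non-inferiority trial a small difference is the desired result, so the same imperfections can help the claim. With intention-to-treat as the only set, a reader could not tell whether HFNC performed as well as NIV or whether some patients never provided a proper comparison. The trial is open-label and clinicians decide how each device is used, so the distinction matters. The usual safeguard is a second analysis, against the same margin, in patients who were eligible and treated as planned. The article's wording leaves no room for one.

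**Working it through.** **Inputs.** From the sample-size section: the 9-point margin; "assuming a baseline failure rate (including modality switch) of 18–23% for each group"; "using an *α* = 0.05 (one-sided) and *β* = 0.20"; computed total 488; target 562, or 281 per arm. Assumed: true failure of 20% (NIV) and 29% (HFNC), exactly at the margin, and dilution shares of 5% and 10%. The article gives no rates for non-adherence, ineligibility or dropout.

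**1. The plan's own figure.** With equal failure p in both arms, total N = 4p(1−p)(1.645 + 0.842)² / 0.09², where (1.645 + 0.842)² = 6.183.

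- p = 0.20: 4 × 0.16 × 6.183 / 0.0081 = 488.5, which matches 488.
- p = 0.18: 450.6 (452 rounded up per arm).
- p = 0.23: 540.7 (542 rounded up per arm).

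The stated size thus corresponds to 20% failure. Also, 488 × 1.15 = 561.2, which rounds up to 562; read as a loss, 1 − 488/562 = 13.2%.

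**2. Chance of declaring non-inferiority.** This is Φ[(0.09 − d)/SE − 1.645], where d is the HFNC minus NIV failure rate and SE = √[p_N(1−p_N)/281 + p_H(1−p_H)/281].

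*No dilution.* d = 0.09, so the result is Φ(−1.645) = 5.0%.

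*A share f of HFNC patients carries the NIV risk with no recorded failure.* Here p_H = 0.29 − 0.09f.

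| f | p_H | SE | (0.09 − d)/SE | False non-inferiority |
|---|---|---|---|---|
| 5% | 0.2855 | 0.0360 | 0.125 | 6.4% |
| 10% | 0.2810 | 0.0359 | 0.251 | 8.2% |

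*A share f is lost in both arms and given one fixed outcome.* The difference shrinks to 0.09(1 − f) whichever outcome is chosen.

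| f | All counted as non-failures | All counted as failures |
|---|---|---|
| 5% | 6.5% | 6.4% |
| 10% | 8.3% | 7.8% |

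*Switching from HFNC only, counted as failure as the endpoint requires.* Here p_H = 0.29(1 − f) + f. At f = 5%, p_H = 0.3255 and SE = 0.0368, so (0.09 − 0.1255)/0.0368 = −0.966 and the result is Φ(−2.611) = 0.5%. Crossover of this kind works against the claim.

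**3. Power of a per-protocol test.** Assume that 488 of the 562 are evaluable, 244 per arm, with equal true rates. Power is Φ[0.09/√(2p(1−p)/244) − 1.645].

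| Failure rate | Power, 244 per arm |
|---|---|
| 18% | 82.7% |
| 20% | 80.0% |
| 23% | 76.3% |

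**The case against.** The strongest reply is that the endpoint already closes the main route by which intention-to-treat misleads in a non-inferiority trial. Changing device is a failure, and step 2 shows that HFNC-only switching lowers the false-positive rate. This stands. A reader might infer from the design that intention-to-treat is anti-conservative here as a general matter; the documents do not support that, because the direction depends on the kind of deviation.

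A reader might also infer that intermittent HFNC and NIV breaks dilute the contrast and that a per-protocol set would remove this. Neither inference is secure. Patients off the device receive standard oxygen, not the other device. If that is less effective, gaps in HFNC would raise HFNC failures and count against the claim, while only NIV breaks would favour it. Both are permitted, so those patients would remain in a per-protocol set.

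Nor is 13% the plan's dropout rate. The increase to 562 also covers nonparametric analysis, and no rate is stated.

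A per-protocol set has weaknesses of its own: exclusions after randomisation can bias in either direction. Intention-to-treat as primary with per-protocol as support is a defensible arrangement, so a rule that both must succeed is a choice and not a requirement.

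Finally, this is a journal article; a full protocol (version 3.0) exists and is not shown, and supportive sets are often left to it or to the analysis plan. That would answer mere silence. The article, however, says that all analyses are intention-to-treat, and another document adding a per-protocol test would contradict it as written.

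**Conclusion.** The point holds in a limited form. The article makes intention-to-treat the sole basis for all analyses of a non-inferiority trial. Four routes can still pull the arms together without a recorded failure: ineligible patients, delivery of the wrong device first, non-adherence beyond what is permitted, and dropouts.

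The size for this trial is unknown. The rise from 5% to 6.4–8.2% is an illustration that rests on assumed dilution of 5–10% of HFNC patients and on true rates exactly at the margin; it is not an estimate of what will happen. Nothing here shows the stated sample size to be wrong, and intention-to-treat remains a proper primary analysis. The weakness is that it stands alone.

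**What to change.** In the statistical analysis section, keep intention-to-treat as primary and make three additions.

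1. **Per-protocol analysis of the primary outcome.** Use the same risk difference, one-sided 95% limit and 9% margin. Include patients who were eligible, started the allocated device and had no major protocol deviation before the event. Patients who switched or were intubated stay in as failures, so that the set does not discard primary events.
2. **Interpretation.** Report both analyses together, and state in advance that disagreement between them weakens the non-inferiority conclusion. Requiring both limits to be below 9% is optional; if it is adopted, joint power cannot exceed that of the weaker test.
3. **Dropouts.** State how they enter the intention-to-treat analysis, and add a sensitivity analysis for missing outcomes. A per-protocol set does not recover those outcomes.

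The cost is one or two extra analyses from data already collected. Per-protocol power would meet the 80% target at failure rates of 18% and 20% but fall to about 76% at 23%, if 488 patients are evaluable. That number is an assumption, and the shortfall at the top of the planning range should be acknowledged.

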## Methods

### Design and setting

This study is a prospective, open-label, multi-center, non-inferiority, randomized controlled trial. It will be carried out in the trauma ICUs of five tertiary university teaching hospitals in China: Northern Jiangsu People’s Hospital (Yangzhou), Peking Union Medical College Hospital (Beijing), The First Affiliated Hospital of University of Science and Technology of China (Hefei), Suqian People’s Hospital of Nanjing Drum-Tower Hospital Group (Suqian), and The Second Affiliated Hospital of Soochow University (Suzhou).

We designed the protocol according to the Standard Protocol Items: Recommendations for Interventional Trials (SPIRIT) statement. This study was prospectively registered at Chinese Clinical Trial Registry on July 24, 2018 (ChiCTR1800017313). Patients are expected to be enrolled during a 36-month period starting in January 2019. A web-based randomization schedule will be used with a block size of 10, and patients will be allocated according to a ratio of 1:1 to the NIV or HFNC groups. Attending physicians and study participants cannot be blinded to their grouping since the devices are clearly different. However, the investigators will be excluded from clinical decisions and will be blinded to the patient group allocations.

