### Outcomes

The primary outcome is treatment failure, defined as intubation and invasive ventilation, or a switch in respiratory support modality (i.e., changing from HFNC to NIV or vice-versa). Detailed information about treatment failure will be recorded from baseline to 28 days after randomization. Secondary outcomes include arterial blood gas (ABG) analysis results [pH, PaO_2_, PaCO_2_, and PaO_2_/FiO_2_] and vital signs [respiratory rate, heart rate, and blood pressure] at 2 and 12 h after initiating NIV or HFNC, as well as the patients’ comfort scores, dyspnea scores, the daily number of nursing airway care interventions, the incidence of pneumonia or pneumothorax, skin breakdown related to the airway device, duration of NIV or HFNC, total ICU and hospital lengths of stay, and 28-day mortality.

In the initial trial registry entry, we set arterial blood gas analysis results and vital signs as the primary outcomes. Considering that the primary purpose of this study was to compare the efficacy and safety of HFNC and NIV for BCT patients, we changed the primary endpoint to treatment failure before starting patient enrollment. The amendments were approved by the study’s steering committee and the ethics review committee of Northern Jiangsu People’s Hospital.

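### The only test stated for percentage outcomes is a test of no difference that does not use the 9% margin, and no non-inferiority criterion is given

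*Protocol article*

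**What the plan says.** The design is fixed in Design and setting: "This study is a prospective, open-label, multi-center, non-inferiority, randomized controlled trial". The Background gives the aim, to "test the hypothesis that HFNC is non-inferior to NIV in reducing treatment failure". Under Outcomes the endpoint is binary: "The primary outcome is treatment failure, defined as intubation and invasive ventilation, or a switch in respiratory support modality".

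The section Statistical analysis and sample-size calculation has two parts.

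- **Sizing.** It works by "assuming a baseline failure rate (including modality switch) of 18–23% for each group and a predefined non-inferiority margin of 9% for HFNC", with one-sided alpha 0.05 and beta 0.20. This gives 488 patients, raised to 562 (281 per arm).
- **Analysis.** Everything is to be by intention to treat. Continuous data get t-tests or Mann–Whitney tests. For percentages the text is "Numeric data will be presented as a percentage (%), using chi-squared or Fisher’s exact probability tests". The only decision rule is "Significance will be set at < 0.05 and all data analysis will be conducted with SPSS 26.0".

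The margin appears in the abstract and in the sizing paragraph. The article gives no confidence interval for the difference in failure rates, no non-inferiority test, and no statement of what result would count as non-inferior.

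**The concern.** The null hypothesis of a non-inferiority trial is that HFNC is worse than NIV by at least the margin. The null hypothesis of a chi-squared or Fisher test is that the two rates are equal. Failing to reject equality does not show that a 9-point deficit has been excluded. A trial with wide uncertainty can give a non-significant test while the data remain compatible with a deficit well beyond 9 points.

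The sample size answers the first question and the stated test answers the second. This matters because non-inferiority on treatment failure is the trial's stated hypothesis. Without a rule tied to the margin, a non-significant p-value could be offered as the answer.

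A smaller point goes with it. The sizing is explicitly one-sided, but the 0.05 rule in the analysis paragraph has no side, so the confidence level for a comparison with the margin is not fixed either.

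**Working it through.** **Inputs from the article.** Failure rate 18% to 23% in each group; margin 9%; alpha 0.05 one-sided; power 80%; allocation 1:1; 488 patients before and 562 after inflation (281 per arm). The absolute-difference scale of the margin is my reading; step 1 supports it.

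**1. Reproducing the plan's figure.** With a true difference of zero and unpooled variance,

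n per arm = 2p(1−p)(z₀.₉₅ + z₀.₈₀)² / 0.09², where (1.645 + 0.842)² ≈ 6.18.

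- p = 0.20: 244.25 per arm, 488.5 in total (490 if each arm is rounded up). This matches 488.
- p = 0.18: 452 in total. p = 0.23: 542 in total.
- With one-sided 0.025 the range is 574 to 688, which does not match.
- Superiority formulas for a 9-point difference give 532 to 608 (one-sided, control rate 18% to 23%) or 674 to 716 (two-sided, control rate 18% to 20%). These do not match either.

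So 488 is a non-inferiority sample size on the absolute scale at one-sided 0.05. The increase to 562 equals 488 × 1.15 = 561.2, rounded up to an even number.

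**2. The stated test when HFNC is worse by exactly the margin.** Exact binomial enumeration, 281 per arm, uncorrected chi-squared, two-sided 0.05 (my assumption, since no side is given). The last column applies the rule that the upper end of the two-sided 90% Wald interval must be below 9 points.

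| True failure, NIV vs HFNC | Chi-squared not significant | Upper limit below 9 points |
|---|---|---|
| 18% vs 27% | 27.1% | 5.0% |
| 20% vs 29% | 29.7% | 5.0% |
| 23% vs 32% | 33.2% | 5.0% |

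Hand check of the middle row:

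- Pooled SE = √(2 × 0.245 × 0.755 / 281) = 0.0363, so the test is non-significant below a difference of 1.96 × 0.0363 = 0.0711.
- Unpooled SE = √((0.29 × 0.71 + 0.20 × 0.80) / 281) = 0.0361.
- Φ((0.0711 − 0.09) / 0.0361) = Φ(−0.52) ≈ 0.30.

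If the 0.05 is read as one-sided, the cut-off is 1.645 × 0.0363 = 0.0597, and Φ((0.0597 − 0.09) / 0.0361) = Φ(−0.84) ≈ 0.20. That is lower, but still four times 5%.

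**3. The stated test when the arms are equal (20% each).** It is non-significant in 95.0% of trials. In 12.8% of all trials it is non-significant while the one-sided 95% upper limit does not exclude 9 points. A significant result favouring HFNC occurs in about 2.5%.

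**4. A single example.** HFNC 73/281 (26.0%), NIV 56/281 (19.9%); difference 6.05 points.

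- Pooled SE = √(0.2295 × 0.7705 × 2 / 281) = 0.0355; z = 1.705; p = 0.088 (0.109 with continuity correction).
- Unpooled SE = 0.0354; upper limit = 0.0605 + 1.645 × 0.0354 = 0.119.

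The test is not significant, yet a deficit of 11.9 points is not excluded.

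**5. Power of a margin-based rule.** Power = Φ(0.09 / SE − z), with SE = √(2p(1−p)/n).

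| Common failure rate | 281 per arm, one-sided 95% limit | 281 per arm, two-sided 95% CI |
|---|---|---|
| 18% | 87% | 79% |
| 20% | 85% | 76% |
| 23% | 81% | 72% |

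For p = 0.20: SE = 0.0337, 0.09 / SE = 2.667, Φ(2.667 − 1.645) = 0.85 and Φ(2.667 − 1.96) = 0.76.

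**The case against.** **The sentence is generic.** It does not name treatment failure, and it would equally cover pneumonia, pneumothorax, skin breakdown and 28-day mortality. A reader might infer that the plan expressly assigns chi-squared to the primary outcome; it does not. What remains is that the primary outcome is binary, the analysis paragraph opens by covering all analyses, and neither an exemption nor a second rule is given.

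**This is detail for the full protocol or analysis plan.** The article is a condensed account, and the choice of interval method is properly left elsewhere. It does fix the margin, one-sided alpha and power, from which a statistician could reconstruct a decision rule. This defence holds only in part. The article is not silent on analysis: it states a test family and a significance rule, and these do not fit its own hypothesis.

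**The analysis could still show non-inferiority.** A reader might infer that the stated test can never do so. That is too strong, because a significant result favouring HFNC would imply it. Under equal rates this happens in about 2.5% of trials, so it cannot serve as the planned test.

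**The false-claim rate measures a misreading.** Correct. Nowhere does the article say that a non-significant test will be taken as non-inferiority, so the 27% to 33% is conditional on that reading. Equally, no stated rule prevents it.

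**The significance level may not conflict with the sizing.** A reader might infer a two-sided test or a 95% interval that contradicts the one-sided sizing. The text states neither, and the 0.05 may simply carry over the one-sided alpha. All that can be said is that the side is not given.

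**Conclusion.** The point holds in this form: the only test and significance rule stated for percentage outcomes do not use the 9% margin, and no non-inferiority criterion is stated. As written, the analysis does not test the trial's hypothesis unless HFNC proves significantly superior. This is a mismatch between what the article states for sizing and what it states for analysis, not merely a missing detail.

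The size is conditional. If non-significance were read as non-inferiority, the false-claim rate at a true 9-point deficit would be 27% to 33%, about five to seven times the planned 5%. This rests on 281 analysed patients per arm, NIV failure of 18% to 23%, an absolute margin, and an uncorrected two-sided chi-squared test at 0.05. A one-sided reading at 20% NIV failure gives about 20%, which leaves the conclusion unchanged.

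A reader might also infer that the trial is too small. The calculations do not support that at the stated one-sided 0.05: the planned 488 is reproduced at 20% failure, and 281 per arm gives 81% to 87% power over the stated range.

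**What to change.** Add a primary-analysis statement along these lines: treatment failure will be compared as the risk difference, HFNC minus NIV, with its one-sided 95% upper confidence limit (the upper end of a two-sided 90% interval); non-inferiority will be declared only if that limit is below 9 percentage points. Name the interval method in the analysis plan.

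Keep chi-squared or Fisher tests for superiority, tested only after non-inferiority is shown, and for categorical secondary outcomes. State the side of the 0.05 level for each use.

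If the team prefers a two-sided 95% interval as the decision rule, the power must be restated: about 76% at 20% failure with 562 patients (72% to 79% over the stated range).

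The cost is a wording change through the amendment route described under Study organization, dated before database lock and before anyone sees results by arm. It needs no new data and no additional patients.

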### Data collection and management

We will collect the personal characteristics of each BCT patient (age, gender, height, and weight), medical history, time of traumatic injury, mechanism of injury, injured organs, imaging results, injury severity score (ISS), AIS chest score, and Sequential Organ Failure Assessment (SOFA) score at enrollment. In addition, we will also collect vital signs (respiratory rate, heart rate, and blood pressure), comfort score, dyspnea score, and ABG results from just prior to initiating HFNC or NIV treatment after patient enrollment (see Table 1). Patients’ dyspnea will be evaluated using the Borg rating scale [16], and patients’ comfort score will be assessed using a 10-cm visual analogue scale, in which 1 means no discomfort and 10 means maximal discomfort [17].

**Table 1 Tab1:** Schedule of enrolment, interventions, and assessments

	Study period					
	Enrolment	Allocation	Post-allocation			Close-out
Timepoint	0	0	2 h	12 h	1–28 days maximum	28 days maximum
Enrolment						
Eligibility screen	×					
Informed consent	×					
Allocation		×				
Interventions						
NIV		×				
HFNC		×				
Assessments						
Baseline variables						
Demographics	×					
Medical history	×					
Mechanism of injury	×					
Injury severe score	×					
Chest AIS score	×					
SOFA score	×					
Outcome variables						
Intubation			×	×	×	
Treatment switch			×	×	×	
Vital signs		×	×	×	×	
Comfort score		×	×	×	×	
Dyspnea score		×	×	×	×	
Arterial blood gas		×	×	×	×	
Number of nursing airway care interventions					×	
Pneumonia or pneumothorax					×	
Skin breakdown					×	
Causes of treatment failure						×
NIV/HFNC duration						×
Hospital length of stay						×
ICU length of stay						×
28-day mortality						×

*HFNC* high-flow nasal cannula oxygen therapy, *NIV* noninvasive ventilation, *AIS* Abbreviated Injury Scale, *SOFA* Sequential Organ Failure Assessment, *ICU* intensive care unit

At 2 and 12 h after allocation, vital signs, ABG results, comfort score, and dyspnea score will be collected. We will then re-collect this information every day until ICU discharge. Moreover, we will separately record each patient’s HFNC or NIV settings, any episodes of skin breakdown related to the airway interface, the number of nursing airway care interventions, and any intolerance to HFNC or NIV due to claustrophobia, excessive air flow or pressure, breathlessness, noise, ocular irritation, headache, or other reasons.

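### The only tests stated for the failure outcome are unadjusted and leave centre and baseline severity unused; they are valid and adequately powered, but a standardised risk difference could be more precise at almost no cost.

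*Protocol article*

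**What the plan says.** The section on statistical analysis and sample size gives one line for percentage data: "Numeric data will be presented as a percentage (%), using chi-squared" or Fisher's exact tests. Other data get t-tests or Mann–Whitney tests. All analyses are by intention to treat. No regression model, covariate or centre effect is named, and no separate sentence sets out the primary comparison.

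The sample size in the same section rests on "assuming a baseline failure rate (including modality switch) of 18–23% for each group" and "a predefined non-inferiority margin of 9% for HFNC", with one-sided alpha 0.05 and 80% power. It continues "We computed a sample size of 488 patients in this trial", and after an allowance for dropout and nonparametric analysis, "562 patients (281 per modality) will be the target sample size for this trial".

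On what is available for adjustment:
- Data collection and management lists age, and "injury severity score (ISS), AIS chest score, and Sequential Organ Failure Assessment (SOFA) score at enrollment". It also lists arterial blood gases taken after enrolment and just before HFNC or NIV starts; Table 1 puts these in the Allocation column.
- Design and setting says of the trial: "It will be carried out in the trauma ICUs of five tertiary university teaching hospitals in China". Randomisation is 1:1 in blocks of 10, and no stratification factor is mentioned.

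**The concern.** In a randomised trial, baseline variables that predict the outcome can be used to narrow the interval around the treatment effect without altering what is estimated. Here several are on the case report form. Some of the intubation criteria are physiological (oxygen saturation, pH, consciousness, respiratory rate), so baseline oxygenation and organ dysfunction plausibly predict failure. The attending physician makes each intubation decision without blinding, so failure rates plausibly differ between centres as well.

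A crude two-by-two comparison leaves that variation in the standard error. The upper confidence limit that is set against the 9-point margin then lies, on average, somewhat higher than it needs to. At stake is a modest amount of power for the non-inferiority conclusion, in a trial whose recruitment has already slipped from December 2021 to June 2022.

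**Working it through.** **Inputs from the article.** One-sided alpha 0.05 (z = 1.645), power 80% (z = 0.842), margin 0.09 read as an absolute risk difference, equal failure rate p in both arms of 18–23%, 488 patients before inflation and 562 (281 per arm) after.

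**Input not in the article.** R², the share of the variance of failure explained by centre and baseline covariates. I take 0 to about 0.14, which corresponds to an AUC of 0.5 to about 0.75.

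**Step 1: reproduce the plan's figure.** Per arm, n = 2p(1−p)(1.645+0.842)²/0.09².
- p = 0.20: 0.32 × 6.183/0.0081 = 244.25, so 488 in total to the nearest patient (490 if each arm is rounded up).
- p = 0.18: 452 in total.
- p = 0.23: 542 in total.

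The stated 488 is therefore the unadjusted formula at 20% failure. Also, 488 × 1.15 = 561.2, which gives 562. The planned power never relied on covariate adjustment.

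**Step 2: power of the crude comparison.** SE = √[2p(1−p)/n] and power = Φ(0.09/SE − 1.645). At p = 0.23 and n = 281, SE = √(0.3542/281) = 0.0355 and power = Φ(2.535 − 1.645) = 81.3%. At 20% it is 84.7%, and at 18% it is 87.1%. With all 562 analysed, the stated 80% is exceeded across the planning range.

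**Step 3: power after adjustment.** Multiply the variance by (1 − R²), so SE = √[2p(1−p)(1−R²)/n]. With 562 patients:

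| Failure rate | R² = 0 | 0.05 | 0.10 | 0.14 |
|---|---|---|---|---|
| 18% | 87.1% | 88.6% | 90.0% | 91.1% |
| 20% | 84.7% | 86.2% | 87.8% | 89.1% |
| 23% | 81.3% | 83.0% | 84.8% | 86.2% |

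The largest gain is 86.2 − 81.3 = 4.9 points. At 23% failure, the distance from the estimate to the one-sided 95% upper limit falls from 1.645 × 3.55 = 5.84 points to 1.645 × 3.37 = 5.54 at R² = 0.10, and to 1.645 × 3.29 = 5.42 at R² = 0.14.

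**Step 4: check by simulation.** A logistic model with five centre terms and one severity score was standardised to a risk difference and compared with the crude difference (562 patients, 20% failure, 1,500 runs per setting):

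| R² (AUC) | Crude power | Adjusted power | Variance ratio |
|---|---|---|---|
| 0 (0.50) | 85.3% | 85.1% | 1.01 |
| 0.03 (0.62) | 85.3% | 85.3% | 0.99 |
| 0.08 (0.70) | 84.3% | 86.4% | 0.92 |
| 0.15 (0.76) | 84.9% | 89.1% | 0.86 |

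With weak predictors there is no visible gain and no material loss. In a separate simulation with a true 9-point deficit and 562 patients, non-inferiority was wrongly declared in 5.05% of runs with adjustment and 4.9% without, so the error rate is not inflated.

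**The case against.** The case against making anything of this is substantial, and most of it stands.

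- **The crude analysis is not wrong.** It is valid under randomisation and matches the basis of the sample size. A reader might infer that the trial is underpowered or that adjustment is needed to reach 80%. That does not follow. It takes both the top failure rate of 23% and the loss of all 74 inflation patients (562 − 488) for crude power to fall to 76.3%, and R² = 0.10 to bring it back to 80.1%. That shortfall comes from sizing the trial at 20%, which is a separate matter.
- **The gain is assumed.** Eligibility narrows the predictors: PaO2/FiO2 between 100 and 200, chest AIS of at least 3, and low Glasgow scores and unstable haemodynamics excluded. The outcome also counts modality switches. The Discussion cites intolerance as the reason for 29% of NIV failures in one study, and nothing in the article shows that severity scores predict intolerance. A gain near nil is possible.
- **The centre term is not obligatory.** A reader might infer that the analysis ignores a randomisation stratum. The article gives a block size but does not say that blocks run within centre, so on its text centre is only a likely prognostic factor.
- **The qualifying PaO2/FiO2 is not listed as a collected item.** The listed blood gas is the one just before treatment starts, so it cannot be assumed to precede allocation.
- **The quoted line is generic, and a fuller analysis plan may exist.** This is fair as to detail. The visible text nevertheless names unadjusted tests and nothing else for a binary outcome, so a plan that adjusts would need to be reconciled with it.

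What survives is narrower: data already collected could sharpen the primary estimate at negligible risk, and the stated analysis does not use them.

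**Conclusion.** The point holds as a missed efficiency gain, not as an error or a shortfall against planned power. The stated tests are unadjusted, and centre, age, ISS, chest AIS and SOFA go unused. Standardised adjustment would add 0 to about 5 points of power at 562 patients, for an assumed R² of 0 to about 0.14. That range is an assumption, because the documents give no prognostic strength. The result also assumes equal true failure rates in the two arms and the margin read as an absolute risk difference. To say that the plan throws away power would claim more than the documents can show.

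**What to change.** State the primary estimate as a covariate-standardised (marginal) HFNC minus NIV risk difference:

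1. Fit a logistic regression of treatment failure on arm, centre, age, chest AIS, SOFA and baseline PaO2/FiO2. Use the eligibility value of PaO2/FiO2 where it is recorded, and otherwise the value measured before treatment starts.
2. Predict each randomised patient's risk under each arm, average over all patients, and take the difference. An adjusted odds ratio would not do, because the margin is on the risk-difference scale.
3. Use a robust or bootstrap interval and compare its one-sided 95% upper limit with the unchanged 9-point margin. A confidence limit is needed in any case: chi-squared and Fisher tests as usually run test equality, not the margin.
4. Keep the crude risk difference as a sensitivity analysis.
5. State whether the blocks of 10 were run within centre. If they were, the centre term follows from the design as well as from prognosis.

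The cost is a paragraph of analysis text and a few lines of code, plus a change to the SPSS sentence if other software is used. No extra patients are needed. The only data question is whether the eligibility PaO2/FiO2 was recorded, and the pre-treatment value serves if it was not. The expected 101 to 129 failures (18–23% of 562) comfortably support nine coefficients besides the intercept (arm, four for centre, four covariates). The model should be fixed before outcome data are seen by arm.
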